### Recruitment

Recruitment took place over 6 months, from December 2023 to May 2024. No critical secular events fell into this study period. Participants who were eligible and agreed to participate in the study will be active in the project for 7 months post-initial recruitment. This time frame starts at the time of recruitment and ends at the final 6-month follow-up time point. Researchers used a purposive sampling technique to recruit participants through multimedia (ie, print and email) and professional network contacts. The study participants were recruited from (1) the main campus and some regional clinical hubs of the Burrell College of Osteopathic Medicine; (2) the University of Texas at El Paso College of Health Sciences, College of Nursing, and School of Pharmacy; (3) federally qualified health centers in the Paso del Norte Region; (4) private provider clinics; and (5) other health care workers and professional network connections that provide training and services to the Paso del Norte region residents. Special attention will be given to recruit practitioners in the specialties of pediatrics, family medicine, and obstetrics and gynecology due to their increased familiarity with vaccines, HPV, and cancer. All participation is entirely web-based. Once the participant is deemed eligible and agrees to participate, they will be provided with a study information sheet outlining that their participation is voluntary, and they can opt out at any time. Participants will be compensated for their time with a US $30 electronic gift card after completion of the initial training session and surveys (~30 minutes). Participants will receive email reminders to complete each of the 2 follow-up survey sessions at 3 and 6 months after completing the initial intervention, as well as an additional US $10 electronic gift card for participating in the follow-up survey sessions (~20 minutes per survey questionnaire).

### Randomization, Treatment Allocation, and Concealment

#### Sequence Generation

After determining eligibility, we will randomize participants on a 1:1 basis to intervention groups (experimental vs control) while controlling for the potential bias introduced by factors of sex, age, and career stage. To achieve this goal, we will use a randomization table within the REDCap (Research Electronic Data Capture; Vanderbilt University) platform to create balanced treatment groups based on these factors and reduce the effect of selection bias [22].

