#### Demographic and Background Questionnaire

The demographic and background questionnaire via the REDCap platform will gather demographic information (eg, age, gender, ethnicity, and income), as well as information about family composition, HPV vaccination status, trusted sources for medical information, general feelings about vaccines, trust in the government, and experiences with the recent COVID-19 endemic [22]. The demographic survey will only be administered at baseline prior to administering the intervention. The demographics survey requires approximately 5 to 8 minutes to complete.

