### Study Outcomes

The chi-square analyses will be used to assess associations between variables reported on the baseline provider knowledge, attitudes, and practice scales. Repeated measures mixed ANOVA with α set to .05 will examine whether change in our outcome variables (self-assessment of the proportions of provider practices, as indexed by the HCP practices scale), provider beliefs (as indexed by the HPV vaccine attitudes scale), and provider knowledge (as indexed by the HPV knowledge scale) is the result of the interaction between the experimental condition (tailored intervention vs active control) and time (at 3 time points) [23]. If no interaction emerges, we will conduct follow-up tests to determine whether any change in our outcome variables are due to one of the factors (experimental condition or time). We will calculate the Mauchly test of sphericity for each ANOVA, and the Huynh-Feldt epsilon test or Greenhouse-Geisser correction to the degrees of freedom of the *F*-ratio will be reported for each significant effect [23-25]. We may use multiple imputation procedures to handle missing data (if applicable).

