### Limitations

This study recruited an internet population of health care providers in the United States–Mexico border region; therefore, findings may not directly translate to other health care provider populations nationally or globally. Furthermore, this intervention did not provide Continuing Medical Education (CME) credit, which would limit uptake outside of an RCT setting. Study participation involved a relatively large time commitment for providers in practice, which worked against recruitment and survey completion. We may, therefore, be somewhat limited in our ability to conduct subanalyses such as comparisons across provider specialties (eg, pediatrics vs family medicine) or other participant characteristics (eg, ethnicity or income level). As we have gathered data from health care providers in medicine, nursing, and pharmacy, different approaches to patient care in these professions may increase variability in the responses obtained. A pretest of HPV and vaccine-associated practices was not done in our study, and the use of solely self-reported data may be incomplete or may contain bias. Our random assignment of participants into control and experimental groups should protect against baseline group differences; however, we will still be able to determine the persistence of any changes in behavior regardless of participant starting point. If any group of providers demonstrates high vaccine recommendation rates at the onset of the study, it will be difficult to determine a statistically significant increase in behavior in response to the intervention. Still, identifying providers with strong recommendation practices will be of benefit to our project. Finally, we anticipate the loss of a limited number of participants through attrition over time for many possible reasons, perhaps reducing the power of our study and our data analysis capabilities at the 3- and 6-month time points.

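### Randomization balances sex, age and career stage but the outcome model names only condition and time, so the between-condition standard error is too wide and its test conservative (the interaction test is unaffected)

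*Protocol article*

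**What the plan says.** Under Sequence Generation, "we will randomize participants on a 1:1 basis to intervention groups" is qualified by "while controlling for the potential bias introduced by factors of sex, age, and career stage". A REDCap randomization table is to be used "to create balanced treatment groups based on these factors and reduce the effect of selection bias". Strata, age cut-points and block size are not given.

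Under Methods, Study Outcomes, a repeated measures mixed ANOVA examines whether change in practices, beliefs and knowledge results from "the interaction between the experimental condition (tailored intervention vs active control) and time". If no interaction emerges, follow-up tests ask whether changes "are due to one of the factors (experimental condition or time"). No section names sex, age or career stage as a term in an outcome model. Analytical Methods refers only in general terms to transformations or model adjustments after assumption checks.

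Three other places bear on this. Limitations states that practices were not pretested. Postassessment calls the first outcome measurement baseline but places it immediately after the intervention. On the background questionnaire, which includes age and gender, the article says: "The demographic survey will only be administered at baseline prior to administering the intervention".

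**The concern.** Balancing the groups on a factor removes that factor's contribution from the difference between group means. A model that omits the factor still leaves its variance in the between-person error term. The reported standard error is then larger than the true sampling variability, and the test rejects too rarely under the null.

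The affected contrast matters in this trial. With no pretest and the first outcome taken after exposure, an effect that appears at once and persists gives parallel group profiles and no condition-by-time interaction. It can be seen only in the condition main effect or in the group comparisons at 0, 3 and 6 months, the times named in the hypothesis. Study Outcomes itself turns to the condition effect when no interaction emerges.

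**Working it through.** **Inputs from the article.** 1:1 allocation; three balanced factors; two conditions; three time points; two-sided α = 0.05; f = 0.15; 80% power; about 110 participants required; 128 recruited. **Not in the article:** R², the correlation ρ among repeated measures, and the sphericity parameter ε.

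**Step 1: the plan's own figure and the test it belongs to.** Analytical Methods sizes the trial on the within-between interaction. With k = 2 groups and m = 3 times, λ = f²·N·m·ε/(1−ρ), with (k−1)(m−1)ε and (N−k)(m−1)ε degrees of freedom. With ε = 1, 80% power needs N = 146 at ρ = 0, 110 at ρ = 0.25 (power 0.806) and 74 at ρ = 0.5. So 110 is attainable but cannot be confirmed from the stated inputs. It concerns the interaction, not the condition effect.

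**Step 2: the interaction test.** This test uses differences within each participant. Sex, age and career stage add the same amount to all three scores of a person, so they drop out of those differences. Entering them as main effects changes nothing here, unless they also predict change over time.

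**Step 3: the between-condition contrast.** Let σ² be the between-person variance of the quantity compared, and R² the share of it that the three factors explain.

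- Standard error reported without adjustment: √(4σ²/N)
- True standard error under near-complete balance, and standard error with adjustment: √(4σ²(1−R²)/N)
- Ratio of adjusted to unadjusted: √(1−R²)
- Actual type I error of the unadjusted test: 2·[1 − Φ(1.96/√(1−R²))]

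| R² (assumed) | √(1−R²) | SE reduction | Type I error, unadjusted |
|---|---|---|---|
| 0 | 1.000 | 0% | 5.0% |
| 0.10 | 0.949 | 5% | 3.9% |
| 0.20 | 0.894 | 11% | 2.8% |
| 0.30 | 0.837 | 16% | 1.9% |

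Put as sample size, 110/(1−R²) means that an adjusted analysis of 110 is worth an unadjusted one of about 122, 138 or 157 for this contrast.

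**Step 4: simulation check.** 4,000 runs per setting, N = 110, permuted blocks of 4 within 8 strata (three binary factors), ρ = 0.5, and R² as the share of variance of each person's mean over time. These settings are assumptions.

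| R² | Reported SE, unadjusted | Actual SD of unadjusted estimate | SE, adjusted | Type I error of condition test, unadjusted / adjusted | Interaction rejection rate, unadjusted / adjusted |
|---|---|---|---|---|---|
| 0 | 0.155 | 0.154 | 0.156 | 0.043 / 0.042 | 0.049 / 0.050 |
| 0.10 | 0.156 | 0.148 | 0.148 | 0.035 / 0.046 | 0.048 / 0.048 |
| 0.20 | 0.155 | 0.138 | 0.139 | 0.025 / 0.045 | 0.049 / 0.049 |
| 0.30 | 0.155 | 0.131 | 0.130 | 0.019 / 0.048 | 0.053 / 0.052 |

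The Monte Carlo standard error of a 5% rate is √(0.05×0.95/4000) ≈ 0.003. The unadjusted estimate is already as precise as the adjusted one; only its reported standard error is too large. For a constant difference of 0.4 SD, power of the condition test, unadjusted against adjusted, was 0.72 against 0.75, 0.75 against 0.82 and 0.75 against 0.86 at R² = 0.10, 0.20 and 0.30.

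**Step 5: single time points.** The same formulas apply, with R² taken for the score at that visit. A single score carries more noise than a mean of three. At ρ = 0.5 the variance of the mean is 0.5 + 0.5/3 = 0.667 of a single score's, so an R² of 0.30 for the mean corresponds to 0.30 × 0.667 = 0.20 at one visit.

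**The case against.** The strongest reply is that the article's named test, and the one behind its sample size, is the interaction, and that test loses nothing. This stands in full. A reader might infer that the whole ANOVA loses precision, or that adjustment would add power to the test on which 110 was based. Step 2 and the last column of the simulation table show otherwise.

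Second, the article is condensed and covariates are commonly listed in an analysis plan. It nowhere says that the analysis is unadjusted, so it would be wrong to conclude that covariates are ruled out. What remains is that the article does set out its model, and the factors it names do not match those it randomizes by.

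Third, R² is assumed, and the degree of balance is unknown because strata, age cut-points and block size are not given. This stands and is why only a range can be offered. A strong link between career stage and recommending the vaccine is plausible but not shown.

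Fourth, the error is conservative. A reader might take a test off its nominal level to mean false positives or bias; neither follows. Nor is chance imbalance in other predictors an uncorrected error, since the unadjusted standard error already allows for it. The statement that "Our random assignment of participants into control and experimental groups should protect against baseline group differences" is fair as an expectation. The documents also give no ground for choosing particular background questionnaire items as further covariates.

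**Conclusion.** The point holds for the between-condition effect only. As described, the model would report a standard error that is too wide for the condition main effect and for the group comparisons at 0, 3 and 6 months. The excess disappears as R² approaches 0. The stated sizes rest on an assumed R² of 10% to 30% for the quantity compared, and the type I error figures also on near-complete balance. The estimate is not biased and false positives are not inflated. What is at stake is a missed effect on the one contrast that can show an immediate, sustained benefit in a trial without a pretest. The change is worth making, but validity is not in question.

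**What to change.** State that sex, age and career stage, coded as in the REDCap randomization table, enter the practices, beliefs and knowledge models as covariates for the between-condition estimate. Do not adjust for any time-0 scale: it is measured after exposure, and adjusting for it could remove part of the effect being estimated. Report the unadjusted estimate as a sensitivity analysis, and claim no gain for the interaction test.

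The cost is one or two sentences and a few degrees of freedom. No new data are needed, since the factors had to be known at randomization. The Results overview says that analysis was in progress as of March 2025, so the statement should record when the covariates were fixed. Keeping to the randomization factors ties the choice to the design rather than to the results.

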#### Concealment

This study is double masked (ie, participant and outcomes assessor). Participants will be randomly assigned to treatment and control groups; they will not be made aware of other participants’ receipt of treatment or control materials. Participants will be asked not to discuss this project outside of the intervention; delivery of the intervention or other educational materials will be internet-based, limiting the ability of participants to interact with one another during the study. Furthermore, to reduce bias in the implementation and assessment of the clinical trial (eg, outcome assessor), participant information and pre-post survey responses will be maintained separately from the assignment and delivery of the intervention.

### Measures

All the survey questionnaire measures or instruments will be made available electronically in English.

#### Screening Questionnaire

Participants completed a screening questionnaire delivered via the REDCap platform to determine their eligibility to participate in the study or intervention [22]. The questionnaire will assess items such as age, geographical location, and health care provider education status (ie, MD, DO, PA, NP, PharmD, or RN) of the potential participant. The questionnaire will also assess their comfort with auditory and visual content in the English language, and if they had prior participation in the earlier phase of this study. The screening questionnaire requires approximately 3 to 5 minutes to complete. Upon successful completion of the screening questions, participants will read and sign the consent form indicating that they agree to participate in the study.

#### Demographic and Background Questionnaire

The demographic and background questionnaire via the REDCap platform will gather demographic information (eg, age, gender, ethnicity, and income), as well as information about family composition, HPV vaccination status, trusted sources for medical information, general feelings about vaccines, trust in the government, and experiences with the recent COVID-19 endemic [22]. The demographic survey will only be administered at baseline prior to administering the intervention. The demographics survey requires approximately 5 to 8 minutes to complete.

#### Postassessment

A post-assessment via the REDCap platform will be administered at baseline (immediately following intervention), 3 months, and 6 months [22]. The post-assessment will include a modified version of the VAKS [13,21] to self-assess factors that influence levels of comfort in discussing HPV-related topics, patient-provider communication about HPV, vaccines, cancer risk, and additional questions designed to evaluate the impact of the interventions and the actual changes in practice in terms of vaccine uptake, patient communication, and vaccine recommendation behavior. Moreover, the outcome variables are included in the post-assessments such as the self-assessment of the proportions of provider practices (as indexed by the HCP practices scale), provider beliefs (as indexed by the HPV vaccine attitudes scale), and provider knowledge (as indexed by the HPV knowledge scale). These will be measured on previously published scales adapted from the VAKS [13,21]. In a previous study that administered the VAKS, Cronbach α ranged from 0.70 to 0.90 for the various scales included in the survey [13]. The post-assessment requires approximately 25-30 minutes to complete.

### Data Collection and Management

All study data will be collected using REDCap [22], a password-secured internet-based software application system developed to design and manage web-based databases and surveys, hosted at The University of Texas at El Paso. All data collected will be deidentified. REDCap will be maintained by the College of Science at The University of Texas at El Paso [22]. Data will remain stored for up to 5 years after completion of the study. Only the study team will have access to the data, as the team has received training on maintaining research data confidentiality, responsible conduct of research, and research ethics with human participants. Data will be accessed through password-protected and encrypted computers.

### Study Outcomes

The chi-square analyses will be used to assess associations between variables reported on the baseline provider knowledge, attitudes, and practice scales. Repeated measures mixed ANOVA with α set to .05 will examine whether change in our outcome variables (self-assessment of the proportions of provider practices, as indexed by the HCP practices scale), provider beliefs (as indexed by the HPV vaccine attitudes scale), and provider knowledge (as indexed by the HPV knowledge scale) is the result of the interaction between the experimental condition (tailored intervention vs active control) and time (at 3 time points) [23]. If no interaction emerges, we will conduct follow-up tests to determine whether any change in our outcome variables are due to one of the factors (experimental condition or time). We will calculate the Mauchly test of sphericity for each ANOVA, and the Huynh-Feldt epsilon test or Greenhouse-Geisser correction to the degrees of freedom of the *F*-ratio will be reported for each significant effect [23-25]. We may use multiple imputation procedures to handle missing data (if applicable).

### Future Directions and Plans for Dissemination

Plans for the dissemination of our findings include publication in peer-reviewed scholarly journals and presentation at scientific conferences, but we are also committed to sharing our data with the community that supports and contributes to this work. For both providers and patients, it is important to base medical decision-making on relevant and up-to-date information. Our findings will also be shared with health care providers in practice and in training at the institutions and locations in which our participants were included. Data will be reported in aggregate form, with no identifying information shared. This data may further be incorporated into the curriculum followed by providers in training in the Paso del Norte region and beyond.

## Results

### Overview

A larger parent grant (NIH/NIMHD 2U54MD007592) was funded in October 2019. Data collection of this subproject, a provider-focused randomized controlled trial (RCT), began in December 2023, with a total of 128 participants recruited by the closing of recruitment in May 2024. Primary data collection was completed in December 2024. As of March 2025, data analysis is in progress, with publication of results anticipated in winter 2025.

### Study Outcomes

#### Provider Practices

Results of the ANOVA model assessing the primary outcome of between-group changes in proportions of provider practices will be summarized and presented in tables and visuals.

#### Provider Beliefs and Provider Knowledge

Results of the ANOVA model assessing secondary outcomes of understanding provider beliefs and provider knowledge will be summarized and presented in tables and visuals.

## Discussion

### Principal Findings

The goal of this RCT was to develop and deploy an educational and professional skills intervention to increase health care provider HPV prevention recommendation scores. This is a critical factor in cancer prevention, and multiple factors contribute to the observation that, while HPV vaccine uptake in our region is higher than in many other regions, it still falls short of national targets. We anticipate finding that health care providers who receive our experimental intervention materials (culturally tailored videos specifically targeting effective HPV vaccine-related communication strategies) will demonstrate improved and more frequent HPV vaccination recommendation practices and behaviors with their patients, as compared to health care provider participants who receive the control materials (standard CDC-issued materials).

### Comparison to Prior Work and Strengths

Our approach to intervention with health care providers is not particularly novel, nor is the intention to increase provider vaccine recommendations since it has been well-established that provider recommendation is one of the most critical factors in patient decisions to get vaccinated [26]. What is innovative in our approach, however, is how we engage with and tailor skills-based training for providers in our region. The initial evaluation of provider knowledge, practices, and beliefs about HPV and the HPV vaccine informed us that HPV-related knowledge among providers is high. An intervention that provides additional education on HPV, the vaccine, and cancer was thus likely to have limited benefit and would not be a valuable use of provider time. In contrast, our intervention focuses on supporting the professional development of providers in the domains of modifying their own behavior and improving communication with patients. Increasing provider awareness of biases in vaccine recommendation and delivery, increasing their comfort in discussions about sexual health topics, and supplying them with tools for addressing patient hesitancy associated with vaccination were determined by our group to be more likely to produce the desired results.

A second way in which our research is innovative is to focus on emerging health care providers. Engaging with this group has the potential to produce multiple positive outcomes, including (1) increased vaccine uptake since many individuals in this group are vaccine-eligible but remain unvaccinated, (2) normalization of vaccine-related discussions in patient care if this becomes a consistent component of provider training, and (3) strengthened vaccine recommendations as the providers themselves serve as role models for vaccination to their patients. Third, we are committed to improving vaccine recommendation behavior by providers that serve a binational, majority-Hispanic population that is medically underserved and faces multiple barriers to vaccination. Previous work has shown that Hispanic women have high HPV vaccine acceptability [27], but this may vary based on age and birth origin [28].

